# Discontinuously supervised aerobic training vs. physical activity promotion in the self-management of type 2 diabetes in older Italian patients: design and methods of the ‘TRIPL-A’ randomized controlled trial

**DOI:** 10.1186/s12877-018-1022-x

**Published:** 2019-01-11

**Keywords:** Diabetes mellitus type 2, Exercise training, Sedentary lifestyle, Habits, Older, Quality of life, Randomized controlled trial, Patient compliance, Exercise referral scheme, Computer-based intervention

## Abstract

**Background:**

Physical activity (PA) has health benefits for people with type 2 diabetes (T2D). Indeed, regular PA is considered an important part of any T2D management plan, yet most patients adopt a sedentary lifestyle.

Exercise referral schemes (ERS) have the potential to effectively promote physical activity among T2D patients, and their effectiveness may be enhanced when they are supported by computer-based technologies.

The ‘TRIPL-A’ study (i.e., a TRIal to promote PhysicaL Activity among patients in the young-old age affected by T2D) aims to assess if realizing an innovative ERS, based on a strong partnership among general practitioners, specialist physicians, exercise specialists, and patients, and supported by a web-based application (WBA), can effectively lead sedentary older T2D patients to adopt an active lifestyle.

**Methods:**

A randomized controlled design will be used, and an ERS, supported by a WBA, will be implemented. 300 physically inactive T2D patients (aged 65–74 years) will be assigned to either an intervention or control arm. Control arm patients will only receive behavioral counseling on physical activity and diet, while intervention arm patients will also undergo an 18-month (3 day/week), discontinuously supervised aerobic exercise training program. The trial will be divided into six three-month periods: during first, third and fifth period, an exercise specialist will supervise the training sessions and, using the WBA, prescribe exercise progression and monitor exercise adherence. Patients will exercise on their own in the other periods.

Patients’ sedentary behaviors (primary outcome), PA level, fitness status, metabolic profile, psychological well-being, quality of life, and use of health care services (secondary outcomes) will be assessed at baseline and at 6, 12, and 18 months from baseline.

Repeated measure ANCOVAs will be used to compare the intervention and control arm with respect to each study outcome measure.

**Discussion:**

Primary and secondary outcome results will allow us to evaluate the effectiveness of an ERS, specifically designed for the management of T2D clinical conditions and supported by a WBA, in promoting PA within Italian primary care settings.

**Trial registration:**

This trial is retrospectively registered under the Australian New Zealand Clinical Trials Registry (reference number: ACTRN12618001164280; registered 13 July 2018).

## Background

The baby boomer generation, one among the largest cohorts of history, is approaching retirement age and the maintenance of the health status and independence of this aging segment of the population (i.e., ≥ 65 years) is currently a major public health concern [1].

Regular physical activity (PA) is one of the main predictors of health and well-being in older people, whereas sedentary behaviors and physical inactivity are associated with an increased risk of over 20 health conditions, including heart diseases, cancer, stroke, and diabetes [2]. Indeed, PA has proven positive effects on people who have stable chronic diseases, such as diabetes, helping to reduce the risk of disability and the use of health care services. Structured PA is now considered an important part of type 2 diabetes (T2D) management plan [3] since it improves blood glucose control and well-being, while reducing diabetes-related complications and cardiovascular risk factors. In addition, reducing sedentary behavior and interrupting prolonged sitting are also recommended to improve blood glucose levels in adults with T2D [4] and such measure have come to be viewed as critical to effective T2D management [5]. In fact, reducing daily sitting time has been shown to yield marked improvements of diabetes clinical goals [6], even when PA engagement is accounted for.

However, despite the well-known benefits of PA and reduced sitting time, most older people adopt a sedentary lifestyle and evidence-based interventions promoting PA largely fail to be translated into practice [7, 8]. This is particularly true for T2D patients, who show low levels of physical activity, high levels of sedentary behaviors [9], and a disappointing low participation rate in diabetes education classes [10]. Indeed, long-term diabetic education interventions do not often yield significant improvements in blood glucose control, regardless of whether they are peer-led in community-based settings [11] or administered by previously trained general practitioners (GP) in clinical settings [12, 13]. Furthermore, existing studies on this topic mostly focus on middle-aged patients, while the literature on older T2D patients is scant (see [14] for a review).

Poor integration among the stakeholders in disease prevention is one of the major causes of the low effectiveness of PA promotion [15]. The literature has shown that exercise referral scheme (ERS) interventions – in which health care professionals refer patients who will benefit from PA to third party services that prescribe and monitor an exercise program tailored to their individual needs – may represent an effective model to promote PA in primary care settings [16, 17]. Specifically, a report from the UK National Institute for Health Research [18] clearly shows that primary care-based ERSs designed for T2D patients lead to a significant improvement in glucose control and a reduction in diabetes complications compared to a non-active intervention comparator. Promoting regular PA in older T2D patients could therefore represent a cost-effective strategy to improve the management of their health condition and their quality of life, while reducing the burden of health care resources. Indeed, findings from other studies (e.g., see [19, 20]) suggest that patients that are referred to PA by GPs are more likely to be active than those who are referred by a visiting specialist. Interestingly, studies have also suggested that the effectiveness of interventions aimed at promoting PA, in both healthy adults [21, 22] and T2D patients [23, 24], may be enhanced when traditional methods are supported by the use of web-based applications (WBA).

To our knowledge, long-term studies implementing an ERS supported by web-based technologies aiming to improve the management of the clinical conditions of older T2D patients have never been conducted in Italy.

## Methods

### Objectives

The ‘TRIPL-A’ study (i.e., a TRIal to promote PhysicaL Activity among patients in the young-old age affected by type 2 diabetes) aims to assess if realizing an innovative ERS based on a strong partnership among GPs, specialist physicians, exercise specialists, and patients, and supported and facilitated by a multi-platform WBA, can effectively lead older sedentary T2D patients to adopt an active lifestyle.

We hypothesize that this ERS will be able to reduce inactivity time and the use of healthcare resources.

Accordingly, the primary objective of the trial is to determine if the ERS reduces sedentary behaviors, while the secondary objectives are to determine if it increases the patient’s physical activity level, fitness status, metabolic profile, psychological well-being, and quality of life, while reducing the use of health care services.

### Design

The ‘TRIPL-A’ is a randomized, controlled, open, bicenter trial, with two parallel groups. The study will be carried out in two urban areas (independent in terms of staff, facilities and participants) in the Marche region (Central Italy): the Diabetology Unit of the IRCCS-INRCA Hospital in Ancona and the Diabetology Unit of the ASUR Hospital of Fabriano (AN). Enrolled patients will be assigned to either the intervention or control arm. The assessments will be performed within the medical facilities, while the exercise training program will be carried out within third party fitness facilities. An overview of the study is shown in Fig. 1.

**Fig. 1 Fig1:**
[figure not shown]
Study design

### Participants’ eligibility

Older T2D patients who meet the inclusion criteria and wish to participate voluntarily will have to sign a written informed consent form before being recruited and any trial procedure occurs. No procedures will be performed until the patient has signed the consent form and been accepted into the trial. Only recruited patients who do not meet any of the exclusion criteria will be enrolled and will participate in the trial.

Trial staff must withdraw enrolled patients at any time if they no longer meet the inclusion and exclusion criteria.

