#### Inclusion criteria

Patients who meet all of the following criteria will be recruited:

- age range (years): 65 to 74;

- suffering from T2D according to ADA criteria [25];

- physically inactive or insufficiently active (i.e., level 1 or level 2 exposure to physical inactivity) according to the WHO framework of health risks quantification [26], as assessed using the results of the *International Physical Activity Questionnaire* (IPAQ) short form.

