### Intervention

Trial intervention will last 18 months during which time concomitant care will be permitted. Patients of both trial arms will be retained as long as they meet the inclusion and exclusion criteria.

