### Assessments/outcomes

Patients’ anthropometrics, sedentary habits, PA level, fitness status, metabolic profile, psychological well-being, quality of life, and use of health-care resources will be assessed, along with other routine assessments, on four separate occasions: at baseline and at 6, 12, and 18 months from baseline (see Table 3). The difference between the intervention and control arms at the 12-month time-point will be considered the main outcome for each measure.

**Table 3 Tab3:** Timing of study assessments

	Screening	Visit 1 baseline	Visit 2 follow-up 1	Visit 3 follow-up 2	Visit 4 follow-up 3
Weeks from randomization	-2	0	24	48	76
Visit window in weeks	–	+ 2	+/− 2	+/− 2	+/− 2
Informed consent	X				
Demographics	X				
Inclusion/exclusion criteria	X	X			
Anthropometric measures		X	X	X	X
Clinical variables		X	X	X	X
Randomization		X			
Lifestyle counseling		X			
Lifestyle informative material		X			
WBA training (only for intervention group)		X			
Blood pressure		X	X	X	X
Registration of laboratory assays		X	X	X	X
LDCW		X	X	X	X
IPAQ (short form)		X	X	X	X
EQ-5D-5L		X			X
PSQI		X			X
Healthcare resource consumption		X	X	X	X
Events					
Adverse events including hypoglycemia		X	X	X	X
New diagnoses		X	X	X	X
Intervention compliance check			X	X	X
Trial completion					X

Notes: *LDCW* long distance corridor walk, *IPAQ* International Physical Activity Questionnaire, *EQ-5D-5L* Euro Quality of Life 5 Dimensional questionnaire, *PSQI* Pittsburgh Sleep Quality Index

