#### Primary outcome measure

Sitting time will be retrieved from the results of the IPAQ short form and computed as average daily minutes of sitting calculated over a one-week period. The IPAQ is a well validated tool [39–43] for assessing both habitual sitting time and physical activity engagement. The IPAQ short form will be interview-administered by trained personnel.

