#### Data analyses

*Intention to treat* analysis will be adopted to account for possible issues related to noncompliance and missing outcomes. Data quality and internal consistency will be assessed *ex-post* using Cronbach’s alpha. In addition, automatic routines will be performed on the data to detect possible outliers, which will be excluded from further analyses. Explorative univariate and bivariate data analyses will then be performed.

For each study outcome, the intervention and control arm will be compared, as the difference between baseline and 12-month time-point, using independent sample t-tests. A mixed-design ANOVA will be used to compare each study outcome between intervention and control arm at the four different time-points, followed by *post-hoc* pairwise comparisons when a significant interaction is found. Participants’ characteristics (e.g., age, sex, fitness status, physical activity level, and metabolic profile) will be used as covariates, and appropriate interaction terms will be assessed and may be included in the model. For all tests, 2-sided *p* values with an α level of significance of 0.05 will be used. Bonferroni’s criterion will be used to adjust the overall α level to correct for multiple tests.

The assumptions of each statistical test will be assessed before analyses and, if not met, either data transformation will be performed or alternative statistical methods will be adopted (e.g., GEE, mixed-models, non-parametric analyses, etc.) will be performed. The residuals and goodness of fit of the models will also be examined.

SPSS Statistics (IBM) and R (R Core Team) software will be used to perform data analyses.

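### Retention is tied to the inclusion criteria, so the rule as written withdraws patients who become active, which is the response the trial seeks

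*Protocol article*

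**What the plan says.** Under Participants' eligibility the protocol article orders: "Trial staff must withdraw enrolled patients at any time if they no longer meet the inclusion and exclusion criteria". Under Intervention it adds: "Patients of both trial arms will be retained as long as they meet the inclusion and exclusion criteria". The rule is therefore mandatory, stated twice, and covers both arms.

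The inclusion criteria it points to include "age range (years): 65 to 74" and being "physically inactive or insufficiently active (i.e., level 1 or level 2 exposure to physical inactivity"), judged from the IPAQ short form. Neither is marked as applying only at entry.

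The Objectives section asks whether the scheme "can effectively lead older sedentary T2D patients to adopt an active lifestyle". On the primary outcome: "Sitting time will be retrieved from the results of the IPAQ short form". On timing: "The difference between the intervention and control arms at the 12-month time-point will be considered the main outcome for each measure". Table 3 repeats the IPAQ at each follow-up visit but lists the eligibility check only at screening and Visit 1. Under Data analyses, an intention-to-treat "analysis will be adopted to account for possible issues related to noncompliance and missing outcomes".

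**The concern.** The activity criterion describes the state that the intervention is meant to end. A patient who moves out of it has responded, and the rule then requires that patient to leave. The questionnaire that shows the response also supplies the primary outcome.

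Retention then depends on response. If the exercise programme raises activity at all, it also depends on arm. The patients left at month 12 would be those still inactive, selected more heavily in the intervention arm, so randomisation would no longer protect the comparison. On the scheduled assessments, a patient classed active at month 6 loses the 12-month primary outcome, and one classed active at month 12 loses the 18-month data. The age criterion works differently: it removes patients at their 75th birthday whatever their arm.

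**Working it through.** **1. The plan's own figure.** Inputs from Sample size calculations: difference 75 min/day, SD 200, two-sided alpha 0.05, power 0.80, 1:1 allocation, 300 enrolled, 20% drop-out.

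n per arm = 2 × (1.96 + 0.8416)² × 200² / 75² = 111.6, so 112, as stated. Evaluable: 150 × 0.80 = 120 per arm. Power at 120 = Φ(75 / (200 × √(2/120)) − 1.96) = 0.828. The design is sound if all randomised patients are followed.

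**2. Removing patients classed active.** The documents give neither the share who become active nor its correlation with sitting time, so both are assumptions shown over a range. Let p be the share of an arm removed by month 6, and rho the within-arm correlation between the activity that triggers removal and sitting time at month 12. Both variables are taken as normal, with rho and the SD the same in both arms.

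- With z the (1 − p) normal quantile, the retained patients' mean activity lies λ(p) = φ(z)/(1 − p) SDs below the arm mean.
- Retained difference = 75 − |rho| × 200 × [λ(intervention) − λ(control)], for rho zero or negative.
- Retained SD = 200 × √(1 − rho² × (zλ + λ²)).
- Power = Φ(retained difference / SE − 1.96), with 120 × (1 − p) patients in each arm.

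λ is 0.109 at 5%, 0.195 at 10%, 0.350 at 20%, 0.497 at 30% and 0.798 at 50%.

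| Removed, intervention vs control | rho | Retained n | Retained difference (min/day) | Power |
|---|---|---|---|---|
| 10% vs 5% | -0.2 | 108 vs 114 | 75 − 40 × 0.086 = 72 | 0.76 |
| 30% vs 10% | 0 | 84 vs 108 | 75 | 0.73 |
| 30% vs 10% | -0.2 | 84 vs 108 | 75 − 40 × 0.302 = 63 | 0.59 |
| 30% vs 10% | -0.5 | 84 vs 108 | 75 − 100 × 0.302 = 45 | 0.37 |
| 50% vs 20% | -0.2 | 60 vs 96 | 75 − 40 × 0.448 = 57 | 0.42 |
| 50% vs 20% | -0.4 | 60 vs 96 | 75 − 80 × 0.448 = 39 | 0.24 |

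These are normal approximations; t-test power is up to about 0.01 lower (0.58 and 0.41 in the third and fifth rows). With zero correlation there is no bias, only lost power.

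**3. Removing patients who turn 75.** If ages are spread evenly over the ten years from 65 to the 75th birthday, 1/10 = 10% turn 75 by month 12 and 1.5/10 = 15% by month 18. On their own, age withdrawals leave 150 × 0.90 = 135 per arm at month 12, above 112. If they come on top of the 20% drop-out, 150 × 0.90 × 0.80 = 108 remain and power is 0.787, against 0.828 at 120.

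**The case against.** The best defence is that the authors meant entry criteria. Table 3 checks eligibility only at screening and Visit 1, and the two retention sentences may be loose drafting. That is plausible, but the sentences are explicit, and one of them says the rule applies at any time. Table 3 conflicts with them and does not cancel them.

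A second defence concerns size, and much of it stands. A patient first classed active at the 12-month visit has already given the primary outcome in that interview, so on the scheduled assessments only month-6 classification costs primary data. By then the prescribed unsupervised training is 3 × 30 = 90 min/week, and the cut-off for leaving the inactive classes lies in a cited source that is not at hand. How many patients would be removed is unknown.

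Some stronger readings are tempting, and the documents do not support them:

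- A reader might infer that a heart attack, TIA or stroke during the trial triggers withdrawal. That exclusion criterion covers only the six months before recruitment, so a later event does not meet it, although other health-related exclusions could still apply.
- A reader might infer that withdrawal at 75 biases the comparison or by itself uses up the sample-size margin. Turning 75 is unrelated to arm, and age withdrawals alone leave 135 per arm.
- A reader might infer that the rule flatly contradicts intention to treat. Nothing says that withdrawn patients' data are discarded. What is missing is any statement that they continue to be assessed, and without that the intention-to-treat label cannot repair the loss.

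**Conclusion.** The rule is wrong as written and should be corrected. It makes retention depend on the response the trial is designed to produce. The direction of the bias is toward no effect, provided that more intervention than control patients become active and that activity and sitting time are negatively correlated.

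The size cannot be derived from the documents. Across the assumed scenarios with negative correlation, a true 75 min/day is seen as anything from about 72 down to 39, with power from 0.76 down to 0.24. No single figure should be quoted as the expected loss. The age criterion is a lesser matter of sample size: power of about 0.83 falls to about 0.79 at month 12, assuming uniform ages and a full 20% drop-out in addition.

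**What to change.** In Participants' eligibility and in Intervention, state that the age and physical-inactivity criteria apply at enrolment only, as Table 3 already implies. Add that a randomised patient who becomes active or turns 75 stays in follow-up and is analysed in the assigned arm, in line with the intention-to-treat statement under Data analyses.

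For the health-related criteria, reconcile the two retention sentences with the Exclusion criteria, Table 3 and Data analyses. Separate stopping the exercise programme from leaving outcome follow-up, and collect outcomes from such patients where the physicians judge it feasible. Which medical conditions stop exercise or particular assessments is left to the physicians. A blanket ban on eligibility-based withdrawal, or compulsory attendance at every visit after a medical stop, would go further than this point requires.

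The cost is a short wording amendment in two places. The visits are already scheduled, and the sample size of 300 needs no change.

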#### Inclusion criteria

Patients who meet all of the following criteria will be recruited:

- age range (years): 65 to 74;

- suffering from T2D according to ADA criteria [25];

- physically inactive or insufficiently active (i.e., level 1 or level 2 exposure to physical inactivity) according to the WHO framework of health risks quantification [26], as assessed using the results of the *International Physical Activity Questionnaire* (IPAQ) short form.

#### Exclusion criteria

Patients who will meet one or more of the following criteria will not be enrolled:

- receiving *β*-blockers therapy or any other drug that could affect heart rate, either at rest or in response to aerobic exercise;

- suffering from chronic obstructive pulmonary disease;

- terminally ill (life expectancy < 6 months);

- suffering from severe cardiovascular disease (including New York Heart Association class III or IV congestive heart failure), clinically significant valvular disease, history of cardiac arrest, presence of an implantable defibrillator, or uncontrolled angina that would interfere with the ability to participate fully in either study arm;

- history of myocardial infarction, transient ischemic attack or stroke in the six months before the recruitment date;

- suffering from any condition that, in the clinical judgement of the principal investigator, might harm the patient if he or she were to participate in the trial.

### ERS and WBA implementation

The ERS to be used in the present study is a physical activity promotion and adoption framework delivered through primary care institutions and implemented within third party facilities. The ERS starts with a GP referral of the eligible T2D patient to the specialist physician of the Diabetology Unit, who will assess her/his clinical status and, in turn, refers the patient to the exercise specialist of the third party facility. The exercise specialist will design a personalized exercise program based on the patient’s medical needs and her/his clinical status, both of which will be provided by the specialist physician. The ERS will also provide feedback through a WBA specifically designed for the study, which will allows the specialist physician and the GP to monitor the adherence of each patient to the exercise prescription made by the exercise specialist.

The WBA will be developed and made available on the Web to patients and trial staff. The WBA will be designed to serve as both the framework on which the ERS is based, and the platform where data are recorded, stored, processed and used by the investigators for the purposes of the trial. Above all, the WBA is designed to enhance and foster the partnership among the study stakeholders, who will have different roles and be based in different locations. In fact, its web-based nature will allow the different stakeholders to access, via a web-browser (therefore regardless the the device used and/or its form factor), to the contents made available according to the privileges granted to each user. All the enrolled patients will have access to generic pages promoting an active lifestyle, providing physical activity and healthy diet guidelines and other useful information on how to self-manage T2D in older adults. Patients enrolled in the intervention arm will also be able to access data generated from their own training (such as adherence to the protocol, average aerobic exercise intensity and duration, motivational feedback based on their training results, etc.). Those data will be made available by the WBA after the automatic processing of the exercise training data entered by the exercise specialists, who will have read and write privileges for all the non-clinically relevant information and all the exercise session report forms of the enrolled patients. GPs and specialist physicians will have access to both the clinical, non-clinical and exercise session data of all the patients they refer to the trial. They will therefore be able to monitor the patient’s adherence to the trial (according to the specific requirements of the study arm to which the patient has been assigned) and readily obtain the information needed to give the patient motivational feedback to improve compliance. The WBA will also allow investigators to store and access patients’ clinically and non-clinically relevant data (copies of patients’ case report forms, test results, and compliance reports; timeline of the trial; randomization; etc.) and to set the range of values of the exercise prescription parameters of the whole training intervention. The WBA will use both the parameters of the exercise prescription and those resulting from each training session in order to constantly provide an updated profile of each patient in the intervention arm. The profile can then be used by the exercise specialists to adjust the exercise type, duration and intensity for the subsequent training session. Finally, the principal investigator will have full privileges, including the ability to export all the data stored in the WBA online database in files to be imported into statistical software.
